## Abstract

**Highlights:**

**Public health relevance—How does this work relate to a public health issue?**
Green space exposure provides extensive benefits for physiological and mental health that will become more important as global temperatures rise and populations continue to urbanize.Small-scale, targeted greening interventions and their influence on temperature-induced cardiovascular stress are not well understood.

**Public health significance—Why is this work of significance to public health?**
This protocol focuses on the development of a comprehensive framework to assess the impact of targeted greening on urban microclimates, ecological function, and cardiovascular resilience.Highlights the work needed to understand how small green spaces can impact users and the surrounding urban form.

**Public health implications—What are the key implications for practitioners, policy makers, and/or researchers?**
Final results will provide insight into the effectiveness of greening interventions on small, underutilized urban lots, which are common in American downtowns.Policymakers can utilize this framework to analyze outcomes related to different green spaces in similar urban environments.

**Abstract:**

The Green Oasis (GRO) Project is a targeted urban greening intervention designed to evaluate the environmental and health impacts of compact, high-density plantings in dense built environments. Initiated in downtown Louisville, the project transformed Founders Square, a 0.64-acre sparsely planted park, into a microforest (“[name] Microforest”), a multilayered planting of 119 trees and more than 200 shrubs. The impact of this intervention is being assessed through a randomized crossover study in which participants walk in the microforest and a nearby impervious parking lot. Physiological outcomes include heart rate, heart rate variability, arterial stiffness, and stress biomarkers measured in saliva, urine, and sweat. Environmental conditions are continuously monitored by fixed and mobile weather stations, air pollution sensors, and biodiversity surveys. Baseline assessments were conducted in 2023 and 2024, with post-planting evaluations now underway (2025–). Power calculations indicate adequate sensitivity (*n* ≈ 40–50) to detect changes in cardiovascular stress responses in participants. Complementary ecological measurements include soil microbiome composition, greenhouse gas fluxes, and avian diversity. This study addresses critical gaps in understanding how small-scale, high-density greening interventions affect cardiovascular resilience, stress physiology, and microclimatic regulation. By integrating environmental, biological, and human health data, GRO establishes a comprehensive framework for evaluating the efficacy of urban microforests as nature-based solutions. The results are expected to inform urban planning, public health strategies, and climate adaptation policies, demonstrating how compact greening interventions can simultaneously mitigate heat, reduce pollution, enhance biodiversity, and promote human wellbeing in dense urban cores.

## 1. Introduction

Extensive evidence indicates that exposure to greenness benefits human health [1]. Individuals living in greener areas show lower levels of stress [2,3,4], depression [5,6,7], insulin resistance [8], diabetes [9,10,11], stroke [12,13], cancer [14,15,16], cardiovascular mortality [17,18,19], and all-cause mortality [19,20], as well as greater longevity [21]. Higher neighborhood greenness has also been associated with better cognitive function, greater physical activity, and reduced obesity risk [22]. Time spent in natural environments is thought to reduce mental fatigue and enhance emotional wellbeing [23,24], underscoring the broad physical and psychological benefits of contact with nature.

Urban greenery is also critical for climate adaptation. Nature-based solutions, including targeted, evidence-based greening interventions, can buffer adverse climatic impacts on health [25,26,27,28,29,30]. Vegetation cools the urban environment through transpiration, whereby water absorbed by the roots evaporates from leaves, lowering ambient temperatures [31,32,33,34]. A study of 93 European cities estimated that increasing tree coverage to 30% could reduce average summer temperature by 0.4 °C and prevent up to 84% of heat-related deaths [35]. In addition to mitigating heat, vegetation also improves air quality, although the mechanisms vary by species, vegetation health, and pollutant type. Modeling and field studies suggest that trees and shrubs can remove ozone [36], polycyclic aromatic hydrocarbons (PAHs) [37], perfluoro carboxylic acids (PFCA) [38], and NO_2_ [39,40,41,42,43,44], and city-wide estimates indicate that green infrastructure could reduce NOx by 35%, PM_2.5_ by 8%, and PM_10_ by 21% [45]. Trees also function as phytoextractors, removing metals such as Cu [46] and capturing metals such as Cd and Pb from the air [47]. Additional ecosystem services include improving soil quality, supporting biodiversity, and reducing stormwater runoff and flooding. Collectively, these benefits highlight the capacity of greenness to mitigate pollution, enhance climate resilience, and promote health, particularly in populated urban areas.

The urgency of urban greening is underscored by climate projections: by 2100, nearly 74% of the world’s population is expected to experience climatic conditions exceeding health-relevant thresholds for at least 20 days annually [48]. Even modest increases in temperature can have widespread consequences [48]. Acute heat exposure induces hemodynamic responses, such as sweating and cutaneous vasodilation, that could compromise cardiovascular function. In addition to temperature, fluctuations in atmospheric pressure and relative humidity are also linked to cardiovascular events [49,50]. Greening strategies may buffer these risks. Controlled studies of walking in forests [51], natural trails [52], and urban green environments [53,54] have demonstrated cardiovascular benefits such as improvements in arterial stiffness [55], reduced sympathetic nervous activity, increased parasympathetic nervous activity, lower heart rate [53], reductions in systolic and diastolic blood pressure [53], as well as lower urinary noradrenaline and dopamine levels, and increases in serum adiponectin [52].

Despite this growing body of evidence, the combined effects of greenness and temperature on cardiovascular health remain poorly understood [56]. Although seasonal variations in the physiological impacts of walking in urban parks have been reported [57], the extent to which urban green spaces mitigate temperature-related cardiovascular stress is unclear. Moreover, the physiological and environmental impacts of small urban plantings have not been studied before. This gap in understanding is critical, as clusters of vegetation may play an especially important role in improving urban environments and buffering heat in heavily built areas. It remains unknown, however, whether small-scale, high-density greening interventions can meaningfully improve microclimates and cardiovascular function.

To address these gaps, we initiated the Green Oasis (GRO) project, designed to evaluate the environmental and health effects of dense urban plantings such as microforests, groves, or woodlets. Primarily, we will evaluate whether dense urban microforest installation modifies heat exposure and acute cardiovascular stress responses. Using a randomized crossover design, we assess the acute cardiovascular effects of walking in an urban setting before and after the installation of a compact, multilayered microforest. We hypothesize that clustered plantings will attenuate urban heat and reduce cardiovascular stress during exposure. Findings from this study are expected to provide novel insights into how small-scale, high-density greening interventions can improve cardiovascular resilience, helping to foster wellbeing in urban populations.

The primary objective of the Green Oasis (GRO) Project is to determine whether, in comparison with exposure to an impervious parking lot, exposure to an urban microforest improves cardiovascular and stress responses (heart rate variability and blood pressure). The secondary objective is to evaluate how exposure to the microforest affects stress biomarkers (catecholamines and cortisol), rumination, anxiety, and exposure to anthropogenic volatile organic compounds (VOC). Our exploratory analyses are to evaluate the effects of the microforest on surrounding environmental conditions (temperature, humidity, particulate matter, NO_2_, black carbon, and noise) and enhance ecological services (avian density, microbiome, etc). Lastly, the integrated objective is to integrate meteorological, ecological, and clinical data to evaluate whether environmental modifications mediate physiological responses. A summary of all research objectives/aims is listed in Table 1.

## 2. Materials and Methods

### 2.1. Study Site and Context

The study site is Founders Square in downtown Louisville. In 1960, a two-story circular building housing an information center and a symbolic “Stonehenge” dedicated to the city’s founders was erected at the site. The building has since been demolished, leaving a one-block parcel that was largely underutilized and dominated by 24 mature oak and cherry trees with scattered shrubs. The central space consisted primarily of grass and brick pavers (Figure 1).

Although previously underused, Founders Square offers an ideal setting for evaluating the environmental and health impacts of greenness. The park lies in one of the densest parts of Louisville, adjacent to the city’s largest residential complexes and served by the second-highest ridership bus line. Across the street, extensive asphalt parking lots provide a clear comparison to the microforest, especially given that downtown Louisville is approximately 54% impervious surface. An estimated 2900 residents live within a half-mile radius of the park, and roughly 31,700 people work within that radius on weekdays. The site is owned by the Louisville Metro Government and has been leased to the University of Louisville for a 30-year period, enabling long-term study of the intervention.

### 2.2. Community Engagement

Community input was central to the design of the microforest. A two-day design workshop and charrette invited nearby residents, downtown workers, and local professionals to collaborate with the contracted design team from Gresham Smith, a landscape architecture, planning, engineering, and architecture firm. The workshop consisted of seven sessions containing roundtable discussions, guest speakers, site visits, and an open house. Researchers working on the [name] Microforest were in attendance to interact with participants and provide feedback to the design firm. Specific themes such as health promotion, heat mitigation, public access, and social connection were discussed. Gresham Smith then compiled results from the workshop/charrette into a summary document, which then informed the final master plan for the space.

The summary document containing feedback from approximately 40 participants informed the initial designs and helped establish key design priorities. Many elements ultimately implemented were first conceived during this workshop, such as the use of Chronolog picture stations, informational signage, and furniture layout/design. General priorities of participants also informed the design, with concepts such as health promotion, natural immersion, and social connection being brought up often. These discussions informed design elements, such as seating placement, layered planting density, public access, signage, and pathway configuration.

To promote transparency and community involvement, dedicated webpages were created to share information about the project. The forest was named the “[name] Microforest” in recognition of the main supporting donor’s family. Webpages were made accessible through QR codes posted on construction signage around the site, and weekly updates were published on the University of Louisville Urban Design Studio website, providing progress reports on both scientific research and construction activities.

### 2.3. Environmental Data Collection

#### 2.3.1. Meteorological Monitoring

To capture meteorological conditions, we deployed two types of weather stations: a WiFi-based “prosumer” system (Tempest Weather Station, WeatherFlow Inc., Santa Cruz, CA, USA) and a research-grade system (Campbell Scientific Inc., Logan, UT, USA). The Tempest stations record a wide range of variables (Table 2) at 1 min intervals and automatically transmit data to a hub and redundantly log in cloud storage. In summer 2023, six Tempest stations were installed, four at the corners of the site and two near the center, allowing measurements across varied shade and ground-cover conditions.

To ensure accuracy and provide long-term monitoring, a Campbell Scientific research-grade station was installed at the site’s center. This station records many of the same meteorological variables as the Tempest, but its temperature sensor is housed in a fan-aspirated shield to prevent stagnation bias. Data are recorded at 1 min intervals and manually downloaded from the datalogger. A fine temporal resolution is used, corresponding to participant exposure periods as part of the human crossover component. Site-wide microclimatic analysis will use hourly and daily data, which can be aggregated into monthly datasets for long-term analysis. Both the Tempest and Campbell systems collected baseline data until site construction began. The central research station and two Tempest units were removed for construction; the research station was reinstalled in December 2024, while the central Tempest stations were permanently eliminated from the final design (Supplemental Figure S1).

During the second round of clinical trials, before the Campbell station was reestablished, a mobile cart system was developed to replicate the fixed-station measurements. This was done to ensure continuity of meteorological measurements when the central fixed station had to be removed during construction. The mobile unit collected equivalent variables at 1 min intervals and was activated at least 30 min before participant arrival to ensure stabilization. In parallel, one researcher wore an AirBeam3 device during participant walks, providing second-by-second measurements of particulate matter (PM_1_, PM_2.5_, and PM_10_).

Both the fixed and mobile Campbell stations were calibrated following manufacturer guidelines. Parallel deployment of the Campbell and Tempest stations allowed for cross-validation during baseline measurements. Data will be acquired both at the microforest site and the impervious parking lot to obtain concurrent measurements. All data will go through quality control screening for missing values, sensor drifts, sensor faults, and anomalous spikes.

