### 2.8. Greening Intervention: The [name] Microforest

#### 2.8.1. Site Preparation and Infrastructure

The intervention began after completion of the first round of baseline testing in Summer 2023. Initial site modifications included the removal of the existing central walkway and the installation of a semi-circular retaining wall, along with a new perimeter walking path (Figure 5). The retaining wall is three feet tall and spans 188 feet, and the wall’s thickness varies from one to two feet to support the weight of the new soil. Benches and lighting were added, and the retaining wall was backfilled with approximately 700 tons of Nugent soil to create a three-foot raised area sloping southward. In addition, metal signage and fins were installed on the south side of the retaining wall to complete the circle, with the signage being 66 inches in height and four inches thick, and the metal fins being 60 inches in height and one inch thick (Supplemental Figure S2). This middle well zone was planted with grass, and mulch was applied along the park’s edges prior to the wave 2 physiological assessment in Summer 2024.

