#### 2.8.2. Planting Design and Species Composition:

The primary phase of greening occurred in Winter 2024 and extended into the following months. A total of 119 trees representing 31 species were planted (Supplementary Table S2), comprising a mix of deciduous (primarily Anacardiaceae, Fabaceae, and Fagaceae families) and evergreen species (mainly Pinaceae). This combination was selected to maximize cooling benefits in a temperate climate and enhance year-round canopy cover. In addition, 242 shrubs and hundreds of herbaceous groundcover plants were installed across the site (Supplementary Table S3). Plant material was sourced from nurseries in multiple states and transported directly to Louisville to minimize storage stress prior to planting.

Trees were planted in close spacing (1–1.5 m apart) to accelerate canopy closure. Shrubs were positioned between rows to form a layered understory, while herbaceous species and groundcovers filled interstitial spaces. This stratified planting scheme was designed to mimic natural forest succession, increase soil infiltration, suppress weeds, and promote early biodiversity. Collectively, these dense plantings are expected to enhance evapotranspirative cooling, mitigate urban heat, and improve ecosystem resilience (Figure 6A,B). Progress of installation is shown in Figure S3.

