#### 2.9.6. Environmental Data Analysis

Meteorological data from the Tempest and Campbell Scientific stations will be quality-controlled to identify and correct erroneous or missing values. Data will be averaged over 15 min intervals for analysis. Two primary analyses are planned: (1) Intra-park analysis—hourly park-wide temperature averages on synoptically stable days (clear skies and calm conditions) will be compared across stations to identify spatial variability due to shading, ventilation, and ground cover. Anomalies relative to park-wide averages will be correlated with solar radiation, wind speed, and ground cover type; and (2) Post-intervention analysis—post-planting data will be compared with baseline measurements to quantify immediate and long-term microclimate effects of the intervention. Long-term trends will be assessed using the central Campbell Scientific station, with monthly statistics computed for all variables. Data will be compared with other stations in the University of Louisville network and with National Weather Service stations to evaluate the microforest’s contribution to reducing the urban heat island effect. Statistical comparisons will use nonparametric tests (e.g., Wilcoxon rank-sum), with significance defined as *p* < 0.05.

Biological and Ecological Data Analysis Avian data will be analyzed in RStudio (v4.3.1) to compare species abundance and diversity across sites ([name] Microforest, University Quad, Nettleroth Sanctuary). Microsoft Excel will support visualization. Surveys will continue after planting to assess temporal changes in avian presence.

Soil flux data (CO_2_ and CH_4_) will be analyzed using multiple linear regression models, with explanatory variables, including vegetation presence, soil moisture, soil temperature, and photosynthetically active radiation (PAR). Variables showing multicollinearity (r ≥ 0.60) will not be included in the same model. Candidate models will be evaluated using Akaike’s Information Criterion corrected for small sample size (AICc), with models within ΔAICc < 2 considered equivalent.

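### In the central Campbell series, the before/after level change is confounded with the station's removal, the site rebuild and reinstallation in the planting season

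*Protocol article*

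**What the plan says.** All references are to the protocol article.

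- **Record before the break (2.3.1).** "Both the Tempest and Campbell systems collected baseline data until site construction began". No calendar date is given.
- **The break (2.3.1).** "The central research station and two Tempest units were removed for construction"; then "the research station was reinstalled in December 2024, while the central Tempest stations were permanently eliminated from the final design". The station was absent during the Summer 2024 visits, when a mobile cart stood in for it.
- **What happened at the centre meanwhile (2.8.1).** The works included "removal of the existing central walkway and the installation of a semi-circular retaining wall", about 700 tons of soil and a three-foot raised area.
- **Planting (2.8.2).** "The primary phase of greening occurred in Winter 2024 and extended into the following months". No single date is given.
- **Cross-check (2.3.1).** "Parallel deployment of the Campbell and Tempest stations allowed for cross-validation during baseline measurements". No repeat after reinstallation is described.
- **Analysis (2.9.6).** The post-intervention analysis is one in which "post-planting data will be compared with baseline measurements to quantify immediate and long-term microclimate effects of the intervention". The next sentence reads "Long-term trends will be assessed using the central Campbell Scientific station, with monthly statistics computed for all variables". Wilcoxon rank-sum is the example given for statistical comparisons.
- **Time series (2.9.5).** The interrupted time series uses weekly values with Fourier terms, and planting is its only interruption.

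**The concern.** The Campbell baseline ends before removal, and all its post-planting data follow reinstallation. Three things change between the two segments: the trees arrive, the ground and structures around the station are rebuilt, and the instrument is taken down and put back. The before/after level change is the sum of all three. The planned model has one step, at planting, so that step takes up whatever the other two contribute.

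More data do not help, because a constant offset does not average out. Calibration to manufacturer guidelines addresses the sensor, not its surroundings. Comparisons with the parking lot, the university network or National Weather Service stations remove shared weather, but not an offset specific to this one station. At stake is whether a cooling (or warming) step at the park centre is credited to plants when part of it comes from the wall, the fill or the reinstallation.

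**Working it through.** The article gives no power or precision figure for this analysis, so there is nothing to reproduce. The question is what the planned contrast can identify.

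**Model.** For week t at the Campbell station:

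Y(t) = a + Fourier(t) + β·P(t) + δ·R(t) + error

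P = 1 from planting and R = 1 from reinstallation. β is the planting step and δ is any offset from reinstallation or the changed ground.

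**Simple comparison (2.9.6).** Baseline weeks have P = R = 0 and post-planting weeks have P = R = 1. Apart from season, the shift is β + δ, and a rank-sum test has no term for δ.

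**Assumed dates, because the article gives too few.** Campbell baseline from July 2023; removal October 2023 or April 2024; reinstallation 2 December 2024; record to September 2027; planting dated from 2 December 2024 to 17 March 2025; two Fourier pairs; independent errors.

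**Step 1: bias if no δ term is fitted.** October 2023 removal, model with a planting step and a post-planting slope, true planting effect zero. The entries are the false planting step in °C.

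| Planting date | δ = 0.2 | δ = 0.4 | δ = 0.8 | Share of δ |
|---|---|---|---|---|
| 2 Dec 2024 | 0.200 | 0.400 | 0.800 | 100% |
| 3 Feb 2025 (9 weeks later) | 0.116 | 0.233 | 0.466 | about 58% |
| 17 Mar 2025 (15 weeks later) | 0.096 | 0.192 | 0.384 | 48% |

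The largest bias in the post-planting slope in any of these runs is 0.0086 °C per year, at δ = 0.8.

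**Step 2: can δ be fitted from the Campbell series alone?** The entries are the variance inflation of the planting step when a δ term is added to a model with the step and seasonal terms. The last two columns add an unbroken corner-Tempest series that shares the planting effect and has no reinstallation step.

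| Planting date | Campbell, Oct 2023 removal | Campbell, Apr 2024 removal | With corners, Oct 2023 | With corners, Apr 2024 |
|---|---|---|---|---|
| 2 Dec 2024 | not estimable | not estimable | 1.2 | 1.6 |
| 30 Dec 2024 | 4.0 | 8.6 | 1.2 | 1.5 |
| 3 Feb 2025 | 2.5 | 4.4 | 1.2 | 1.4 |
| 17 Mar 2025 | 2.0 | 3.0 | 1.2 | 1.3 |

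Where the step is estimable from Campbell alone, its standard error grows by √2.0 ≈ 1.4 to √8.6 ≈ 2.9. With the corner series the factor is √1.2 ≈ 1.1 to √1.6 ≈ 1.3.

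**Step 3: what the corner bridge assumes.** If planting changes the centre by β_c and the corners by β_k, the Campbell-minus-corner change estimates δ + (β_c − β_k). It isolates δ only if planting acts about equally at both. If the centre cools more than the corners, subtracting this quantity removes real planting effect.

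**Scale.** The Introduction cites 0.4 °C average summer cooling from 30% tree cover across 93 European cities. An assumed offset of 0.1 to 0.3 °C would be 0.1/0.4 = 25% to 0.3/0.4 = 75% of that. The article supports neither the offset nor the transfer of a city-scale figure to one park, so this shows only that small offsets would matter.

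**The case against.** The strongest reply is that the plan is broader than one station and that no offset is documented. Much of this stands.

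- **Complete aliasing.** A reader might infer that offset and planting can never be separated. That is exact only for the level change in the Campbell series with coincident dates. Planting ran over months and has no single date. A few weeks' separation makes the step estimable, though imprecise, and only if a second term is fitted.
- **Bias in the long-term trend.** A constant offset leaves the slope after 2024 almost unchanged. As trend over time, what the station is named for largely survives.
- **Aim 3 resting on this station alone.** It does not. Sections 2.9.5 and 2.9.6 and Table 1 also bring in Tempest data, the parking lot and regional sources, and the pollutants are not weather-station variables.
- **A moved or raised station.** The text says reinstalled, not relocated, and the station map (Supplemental Figure S1) is not shown. The documented change is to the surroundings.
- **Ground works as intervention.** Section 2.8 describes the works under the greening intervention. On that reading their effect is not bias, and only an instrument or placement offset is. But 2.9.5 dates the interruption to planting, so the planned estimate would still credit the works to planting.
- **Existing safeguards.** Data are screened for drifts and faults, and a calibrated cart measured in Summer 2024. The cart is described for participant visits, and no co-location with the fixed station is described. Screening as described does not mention a step at reinstallation.
- **Condensed article.** Homogenisation details may sit in a fuller plan. The station, the contrast and the single interruption are nevertheless fixed here.

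**Conclusion.** The point holds for the level change in the central Campbell series. As written, the plan would neither detect an offset specific to this station nor separate it from planting. Under the dates assumed above, 48% to 100% of a constant offset enters the time-series planting step; in the simple baseline versus post-planting comparison all of it does. The post-2024 slope is essentially unaffected.

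The size and direction of any offset are unknown, and none is documented. The conclusion rests on reading Winter 2024 as the winter beginning in late 2024. That fits the August 2024 photograph of the backfilled wall (Figure 5) and post-planting evaluation from 2025. The remedy rests on the four corner Tempest units having stayed in place and kept logging; they are not listed as removed, but the article does not say so outright.

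This is worth correcting within exploratory Aim 3. It does not touch the randomized site comparison of heart rate variability and blood pressure.

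**What to change.** For exploratory Aim 3, state in the analysis plan:

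1. The dates of removal, reinstallation and planting, and whether the station's position, height or ground surface changed.
2. A repeat of the Campbell versus corner-Tempest cross-check after reinstallation, compared with the baseline cross-check.
3. The before/after change at the four corner Tempest units, reported beside the Campbell result.
4. A construction/reinstallation term in the interrupted time series, estimated with the corner series, and the assumption of a similar planting effect at corner and centre stated openly.
5. The change in Campbell-minus-corner difference on overcast, windy nights as a sensitivity analysis only. It should not be subtracted automatically: it misses daytime exposure effects and may remove part of a real planting effect.
6. If the break cannot be separated, attribution of the level change to the whole site rebuild and not to planting alone.

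If the corner units kept logging, the cost is a short extra analysis of existing data and a wider interval for the planting step: about 1.1 to 1.3 times the standard error under the assumptions above.
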